#### Secondary outcomes

Abnormal Eating Behavior Questionnaire (AEBQ) will be applied to investigate the frequency and the developing order of abnormal eating behavior. The 27-item AEBQ Chinese version is comprised of five domains of behaviors, namely swallowing disorders, appetite changes, food preferences, eating habits, and other abnormal eating behaviors. The single item score was calculated as frequency (ranging from 0 to 4, representing from never happen to more than once per day) * severity (ranging from 1 to 3, representing mild, moderated, and critical influence on eating behavior, respectively). The Cronbach’s *α* of frequency, severity, and the total score of AEBQ-Chinese version were 0.73, 0.74, and 0.74, respectively [22].

Mini-Nutritional Assessment-Short Form (MNA) is employed to screen malnutrition. MNA is comprised of 6 items, including weight loss, body mass index (BMI), acute diseases, mobility, mental disease, and dysphagia or anorexia. The score range of MNA is from 0 to 14, MNA<11 suggests being at risk of malnutrition, and MNA<8 indicates malnourished status. The specificity and sensitivity of MNA in predicting malnutrition were 88.8% and 85.6%, respectively [23].

The activity of daily living will be evaluated using Barthel Index (BI), a 10-item rating scale assessing individual functional capacity. The score range of BI varies from 0 to 100, and the higher BI score reflects the greater daily living activity. The empirical study yielded the test-retest reliability and interrater reliability of BI were 0.89 and 0.95, respectively [24] .

Adverse events and unexpected symptoms that happen during the intervention timeframe will be recorded and analyzed. The safety coefficient of each group is calculated as follows. Safety coefficient = (the number of adverse events/the number of engaged participants) * 100%.

The proposed study will use attendance rate to evaluate participants’ intervention adherence. Individual attendance rate = (actual number of participation/total number of intervention session) * 100%.

### Sample size

The sample size was calculated based on the comparison of WST. By using G*Power 3.1 software, we set a significant difference of 14.2% (74.2% in the experimental group and 60.0% in the control group), an alpha error of 0.05, a beta error of 0.80, and the effect size *f* = 0.32. After calculation, a total sample size of 78 was required. To accommodate for a 20% attrition rate and other confounding factors, we recruited 100 participants. After obtaining informed consent, each involved hospital was allocated to the intervention group or to the control group in a 1:1 ratio.

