#### Primary outcomes

Water Swallowing Test (WST), a five-level water drinking test, will be used to determine the effectiveness of SST. Evaluators observed individual reactions after drinking 30 ml of water (complete recovery: swallowing without cough; improved swallowing function: occasional choking, and invalid: unchanged or worse swallowing function). Effective rate = (completed recovery + improved swallowing function)/total cases in each group *100%. The sensitivity and specificity of WST ranged from 34.8 to 55.7% and 78.9 to 93.2% in older adults [20].

On basis of WST, Standard Swallowing Assessment (SSA) will be performed to evaluate the severity of dysphagia. The score of SSA ranged from 18 to 46, and a high SSA score reflected serious dysphagia. SSA exhibited a specificity of 0.90 and a sensitivity of 0.97 in detecting dysphagia, with positive and negative predictive values of 0.92 and 0.96 [21].

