### Statistical methods

Exploratory data analysis and Shapiro-Wilk tests will be performed to determine the normality of data distribution. Continuous variables will be expressed as means with standard deviations or medians with interquartile ranges; mean differences will be expressed from baseline to the end of the study. For categorical variables, counts and percentages will be presented, and between-group comparisons at baseline will be tested with the *x*^*2*^ test [25]. Between-group differences at baseline, and in the change from baseline to the end, will be tested with repeated measure analysis of variance. An analysis of covariance will be used to adjust for baseline cognitive functioning. Paired *t*-tests will be performed for between-group comparisons from the baseline to the end. The level of significance will be set as a two-sided *P* value less than 0.05. Data analysis will be conducted using SPSS version 20.0 with intent-to-treat analysis (ITT) and per-protocol (PP) analysis. The results of the ITT analysis will be compared with those of the PP analysis to determine the consistency.

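### The planned 78 participants do not follow from 74.2% vs 60.0%: those rates give about 26-27% power, not 80%, because the effect size entered (f = 0.32) is about twice what they imply.

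*Protocol article*

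**What the plan says.** The Sample size section of the protocol article names its basis: "The sample size was calculated based on the comparison of WST". The planning difference is "a significant difference of 14.2% (74.2% in the experimental group and 60.0% in the control group"). The error rates are given as "an alpha error of 0.05, a beta error of 0.80", followed by an effect size f of 0.32. The result is that "a total sample size of 78 was required", and this is raised to 100 for 20% attrition.

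Under Primary outcomes, the WST result is a proportion in each group: "Effective rate = (completed recovery + improved swallowing function)/total cases in each group *100"%. The Sample size section does not say whether alpha is one- or two-sided. Statistical methods does: "The level of significance will be set as a two-sided *P* value less than 0.05". Trial design gives 1:1 allocation.

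**The concern.** The section gives the planning effect twice, once as a pair of rates and once as f, and does not show how one leads to the other. For two equal groups, a gap between 60.0% and 74.2% is a small standardised effect, whereas f = 0.32 is a medium-to-large one equal to a standardised difference of 0.64. They cannot both describe the same planning assumption, and the sample size depends on which was used.

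WST is a primary outcome and the only stated basis for the sample size. A reader is told that the trial has 80% power to detect 14.2 points. If it has much less, a non-significant WST result says little about whether the training works, yet the stated power invites the reader to take it as evidence of no effect.

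**Working it through.** **Inputs.** Rates p1 = 0.742 and p2 = 0.600, alpha 0.05, f = 0.32, N = 78, 20% attrition and 100 recruited (Sample size). Two-sided level (Statistical methods). 1:1 allocation (Trial design). The beta of 0.80 is read as power 0.80.

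**1. Reproducing 78 from f = 0.32.**
- Chi-square test, 1 df, w = 0.32: noncentrality 78 × 0.32² = 7.99, power 80.7%. The smallest N for 80% is 77, or 78 with equal arms.
- Two-group ANOVA, f = 0.32: power 79.7% at N = 78 and 80.7% at N = 80.

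So 78 follows from an effect size of 0.32. The attrition step is also sound: 78/0.8 = 97.5, i.e. 98, rounded up to 100.

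**2. Effect size implied by the rates.**
- Cohen's h = 2·arcsin(√0.742) − 2·arcsin(√0.600) = 2.076 − 1.772 = 0.304, and h/2 = 0.152.
- w = (0.142/2)/√(0.671 × 0.329) = 0.071/0.470 = 0.151, where 0.671 is the mean rate.
- f = (0.142/2)/within-group SD = 0.153.

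All three are about 0.15, so 0.32 is about 2.1 times too large. With 60.0% in the control group, w = 0.32 would mean about 88% in the experimental group.

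**3. Sample size the rates require.** Pooled-variance formula:

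n per arm = [1.96·√(2 × 0.671 × 0.329) + 0.842·√(0.742 × 0.258 + 0.600 × 0.400)]² / 0.142²

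= [1.96 × 0.6645 + 0.842 × 0.6568]² / 0.142² = 170.7, i.e. 171 per arm.

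The total is 342 evaluable, and 342/0.8 = 427.5, i.e. 428 to be randomised. With a continuity correction the evaluable total is 370.

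**4. Power for 74.2% vs 60.0% at the planned sizes.** Power = Φ[(0.142·√n − 1.96 × 0.6645)/0.6568].

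| Analysed | Per arm | Power, two-sided 0.05 |
|---|---|---|
| 78 | 39 | 26.3% |
| 80 (100 less 20%) | 40 | 26.9% |
| 100 (no loss) | 50 | 32.5% |

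At 39 per arm other methods agree: arcsine 26.8%, noncentral chi-square 26.5%, exact enumeration of the uncorrected chi-square 27.1%. Fisher's exact test gives 18.9%.

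**5. What 40 per arm can show.** Solving the same formula for 80% power against 60% gives an experimental rate of 87.2%, a difference of about 27 points. At the planned rates the expected 95% CI half-width is 1.96·√[(0.742 × 0.258 + 0.600 × 0.400)/40] = 0.204. That is about 20 points, wider than the 14.2-point effect itself.

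**6. Other readings of the inputs.**
- One-sided alpha: 135 per arm (270 in total), and 37.7% power at 78.
- Beta taken literally as 0.80 (power 0.20): 28 per arm (56 in total).

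Neither gives 78.

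**The case against.** The strongest objection is that the section names no test. The symbol f belongs to analysis of variance, and Statistical methods plans repeated-measures ANOVA, so a power figure for a single comparison of two proportions may not be what was meant. The protocol gives no within-person correlation, so the values used here are assumptions.

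- *Between-group effect, three time points, f = 0.152, N = 78.* Power is 63%, 37% or 30% for correlations of 0, 0.5 or 0.8. None reaches 80%.
- *Group-by-time interaction.* With the same f, power at 78 is 53% at correlation 0 but 84% at 0.5, so on this test 78 could suffice. That still does not rescue the stated calculation. An f taken from two endpoint rates is not an interaction effect, the effective rate is one proportion per group, and at correlation 0.5 the stated f = 0.32 would need only 18 participants, not 78.

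What stands is that the 26-27% figure belongs to a two-sided test of two proportions and should be reported as such. Two-sidedness is likewise inferred from Statistical methods.

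The 26-27% also assumes 78-80 analysed. With intention-to-treat and no missing outcomes it is 32.5%, so the planned effect would be missed about two times in three rather than three in four.

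Finally, the trial calls itself exploratory and has a second primary outcome, the Standard Swallowing Assessment. This softens the consequence, since WST is not the only evidence on swallowing function. An exploratory trial may be small, but the label does not make a formal calculation with incompatible inputs correct.

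**Conclusion.** The concern holds. The Sample size section is wrong as written: its rates, its effect size and its total cannot all be true. The total of 78 matches f = 0.32, while the rates imply about 0.15 and need 342 evaluable participants, more than four times as many (342/78 = 4.4). Power for the stated difference is about 26-27% with 78-80 analysed and at most 32.5% with all 100.

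These figures assume individual 1:1 allocation, a two-sided 5% level and a single comparison of effective rates. The contradiction among the inputs does not depend on the choice among the two-proportion methods tried, or on sidedness. Why 0.32 was entered is not known. A d- or h-type effect of about 0.30 entered as f would be a plausible slip, but nothing in the document proves it and the conclusion does not need it. The beta of 0.80 is a labelling error with an obvious meaning and adds little by itself.

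**What to change.** Revise the Sample size section as follows:

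- Replace the beta of 0.80 with power 0.80 (beta 0.20), and state that alpha is two-sided.
- Name the test to which the calculation refers.
- Delete the claim that 78 participants suffice for a 14.2-point difference, and remove f = 0.32 as the effect size for these rates.
- State that 100 randomised, with 80 evaluable, gives about 27% power for 74.2% vs 60.0% and 80% power only for a difference of about 27 points (about 87% vs 60%).
- Say that the WST effective rate will be presented as a between-group difference with its 95% CI, expected to be about ±20 points.

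Moving f = 0.32 to the Standard Swallowing Assessment because the total then fits is not a remedy: the protocol gives no expected difference or standard deviation for that score.

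The cost is protocol wording only. No extra enrolment is needed, but the stated power becomes much less favourable. If the sponsor prefers to keep 80% power for 14.2 points, 428 must be randomised. Against the roughly 521 eligible patients estimated under Recruitment, that means about 82% uptake (428/521).

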## Methods

### Trial design

This training program is a multi-center, exploratory, single-blinded, parallel randomized controlled trial (RCT) with a 4-week follow-up period. All stages are conducted according to the SPIRIT reporting guidelines [18]. Treatments administered will be allocated randomly according to a 1:1 ratio by an online random-number generator of SPSS software by research assistants who are not involved in assessment and intervention. The researcher will then offer the research assistants in each hospital the allocation of groups with sequentially numbered opaque, sealed, and stapled envelopes. Then, the training schedule will be conducted based on this research protocol.

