### Study settings and participants

This trial will be conducted in three major public psychiatric hospitals in Guangdong, China—Affiliated Brain Hospital of Guangzhou Medical University (GZ), the Third Hospital of Jiangmen (JM), and the Third Hospital of Yuebei (YB). This research has obtained ethical approval from the Institutional Review Board of GZ (approval number: 2021070), and the research will be conducted with the consent of each hospital’s executives. Before allocation, informed consent will be obtained from all participants.

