### Interventions

Participants will be randomly allocated to either the SST group or the control group. The flow chart of this study was presented in Fig. 1*.* Participants in the control group will receive routine dysphagia care, while the intervention group will receive SST based on routine care five times a week for four weeks. The process includes five sections of swallowing muscles, and each section will provide step-by-step training, according to the difficulty experienced by the participant. Each section will be divided into three levels of difficulties, starting from level 1(easy) through level 2 to level 3 (difficulty) each time. As presented in Fig. 2, the instructional video will be shown to the patient along with one-to-one guidance.

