### Recruitment

The proposed study will recruit AD patients hospitalized in sampling sites. Water Swallowing Test, an indispensable part of the medical assessment conducted after admission, will be applied to scan the swallowing function of AD patients. Patients who meet the inclusion criteria will be invited to participate in this study. The proposed study will recruit participants in three public tertiary psychiatric hospitals, namely Guangzhou, Shaoguan, and Jiangmen City, in which the annual number of admission of AD patients were approximately 380, 200, and 320, respectively. Based on the pilot investigation, the prevalence of dysphagia among AD patients was 38.6%; thus, we estimate that the number of participants who meet inclusion criteria is (380 + 200 + 320) * 1.5 years * 38.6% ≈ 521>100. Additionally, the participants’ recruitment timeframe would be extended if necessary.

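### The sample size section names the hospital as the unit of allocation, contradicting the individual randomisation described elsewhere; three hospitals cannot be split 1:1

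*Protocol article*

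**What the plan says.** The protocol article describes allocation in four places.

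- **Trial design:** a parallel randomised trial in which "Treatments administered will be allocated randomly according to a 1:1 ratio by an online random-number generator of SPSS software". The researcher will then "offer the research assistants in each hospital the allocation of groups with sequentially numbered opaque, sealed, and stapled envelopes".
- **Study settings and participants:** "Before allocation, informed consent will be obtained from all participants".
- **Interventions:** "Participants will be randomly allocated to either the SST group or the control group".
- **Sample size:** once consent is obtained, "each involved hospital was allocated to the intervention group or to the control group in a 1:1 ratio".

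On the number of sites, Study settings states: "This trial will be conducted in three major public psychiatric hospitals in Guangdong, China". The Recruitment section gives their sizes: "the annual number of admission of AD patients were approximately 380, 200, and 320, respectively".

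The Statistical methods section names repeated-measures analysis of variance, analysis of covariance adjusting for baseline cognitive functioning, and paired t-tests. Neither it nor the Sample size section mentions clusters, an intraclass correlation (ICC) or a design effect.

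**The concern.** The first three places make the participant the unit of randomisation. In the Sample size section the grammatical subject is the hospital. These are two different designs.

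The unit of allocation determines what the trial can claim. If participants are randomised within hospitals, the individual-level sample size and analysis have the right form. If whole hospitals are assigned, one arm is a single hospital, any difference between hospitals in patients or routine care is inseparable from treatment, and an analysis that treats 100 patients as independent is invalid. A reader who meets only the Sample size section, such as a systematic reviewer classifying the design, could record this as a cluster trial analysed as if it were not one.

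**Working it through.** **1. The plan's own figure.** Inputs from the Sample size section: f = 0.32, alpha 0.05, and 0.80 (printed as beta error, read here as power). The two-sided level comes from Statistical methods. For two groups d = 2f = 0.64.

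n per arm = 2 × (1.960 + 0.842)² / 0.64² = 2 × 7.85 / 0.4096 = 38.3, rounded up to 39, so 78 in total. The exact noncentral F calculation gives 79. Allowing for 20% attrition, 78 / 0.80 = 97.5, rounded up to 98, against the stated 100.

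So 78 reproduces as an individual-level calculation with no allowance for clustering. It fits participant randomisation and does not fit hospital allocation.

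**2. Can three hospitals be allocated 1:1?** No. If both arms are used, the only split is 2:1. Nor does it give equal arms in patients if recruitment follows the stated admissions (380, 200 and 320, total 900; shares 42.2%, 22.2% and 35.6%):

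| Hospital alone in one arm | Approximate split of 100 patients |
|---|---|
| Guangzhou (380) | 42:58 |
| Jiangmen (320) | 36:64 |
| Shaoguan (200) | 22:78 |

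**3. What the literal reading would do to inference.** There are three ways to choose the hospital that stands alone, so a randomisation test cannot give P below 1/3. If it is also random which arm gets the single hospital, there are six assignments and the two-sided minimum is 2/6 = 1/3. A t-test on hospital means has 3 − 2 = 1 degree of freedom and a two-sided 5% critical value of 12.7.

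**4. Design effect under the literal reading.** The article gives no ICC, so a range of 0.01 to 0.10 is assumed, with equal hospitals of m = 100/3 = 33.3. Design effect = 1 + (m − 1) × ICC.

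| Assumed ICC | Design effect | 78 becomes | Effective size of 100 |
|---|---|---|---|
| 0.01 | 1.32 | 104 | 76 |
| 0.02 | 1.65 | 129 | 61 |
| 0.05 | 2.62 | 205 | 38 |
| 0.10 | 4.23 | 331 | 24 |

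Even these figures understate the difficulty. With one hospital in an arm, adding patients does not separate treatment from hospital.

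**5. Which reading fits the text?** A numbered series of sealed envelopes at each hospital has no purpose if the whole hospital has one arm. Participant consent precedes allocation, both in Study settings and in the opening of the disputed sentence itself. The sample size is unclustered. All three support individual allocation within each hospital.

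**The case against.** The strongest reply is that this is a slip of wording. The sentence most likely meant that participants in each involved hospital were allocated 1:1, and on that reading no number in the plan changes. That stands, and it limits the point to a contradiction that needs correcting. It does not remove the point: the sentence is wrong as printed, on a defining feature of the design, and nothing else in the article corrects it.

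Two stronger readings are tempting, and the document supports neither.

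- **That this is really a cluster trial that must be redesigned or re-powered.** A reader might infer this, especially as the sentence is in the past tense and recruitment began in March 2022. But the same section also reports recruiting the 100 participants in the past tense, although Trial status anticipates completion in March 2023, so the tense shows little. The 1/3 P value and the design effects apply only if hospitals were in fact assigned whole, which the rest of the article contradicts.
- **That the randomisation is unstratified and exposes the trial to imbalance between sites.** With one simple list for 100 patients, the chance of a 45:55 split or worse would be 37%. But the article nowhere says that there is a single list or no stratification. Envelopes at each hospital are at least as compatible with 1:1 allocation by site. A condensed article commonly leaves such details to the full protocol or analysis plan.

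**Conclusion.** The contradiction is certain: the Sample size section names the hospital as the unit of allocation, and Trial design, Study settings and Interventions describe participants. The impossibility of a 1:1 split of three hospitals is also certain.

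The consequences depend on what was done. On the probable reading, individual randomisation within hospitals, this point changes neither 78 nor 100. On the literal reading, treatment is confounded with hospital, no randomisation test can reach 0.05, and the sample size and unclustered analysis are invalid. The design effects of 1.32 to 4.23 rest on an assumed ICC and on equal hospital sizes.

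Saying that 78 needs no cluster inflation does not endorse it in other respects. Whether f = 0.32 follows from the stated response rates is a separate question.

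**What to change.** 1. Confirm from the allocation records which unit was randomised.
2. If it was the participant, correct the sentence in the Sample size section to agree with Trial design and Interventions, for example: *After informed consent, participants in each hospital were individually allocated to the intervention or control group in a 1:1 ratio.* This costs one sentence. The allocation procedure itself should not be altered, with recruitment already begun, in order to cure an error of wording.
3. If any hospital was assigned whole to one arm, the report must say so and make no claim of individual randomisation.
4. If the envelopes were prepared by hospital, include hospital as a term in the between-group models. With three hospitals this costs up to 3 − 1 = 2 degrees of freedom. It is a low-cost addition, and may already be in the full protocol or analysis plan.

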### Recruitment

The proposed study will recruit AD patients hospitalized in sampling sites. Water Swallowing Test, an indispensable part of the medical assessment conducted after admission, will be applied to scan the swallowing function of AD patients. Patients who meet the inclusion criteria will be invited to participate in this study. The proposed study will recruit participants in three public tertiary psychiatric hospitals, namely Guangzhou, Shaoguan, and Jiangmen City, in which the annual number of admission of AD patients were approximately 380, 200, and 320, respectively. Based on the pilot investigation, the prevalence of dysphagia among AD patients was 38.6%; thus, we estimate that the number of participants who meet inclusion criteria is (380 + 200 + 320) * 1.5 years * 38.6% ≈ 521>100. Additionally, the participants’ recruitment timeframe would be extended if necessary.

